#### Reliability

Split-half reliability of the bias scores will be assessed by correlating bias scores based on odd versus even trials [see e.g., 54, 55, 84]. Importantly, only bias scores with at least acceptable reliability (Spearman-Brown corrected reliability > 0.7) will be analyzed and reported. In addition, to rule out that the results are influenced by the subjective rating of the participants’ responses, interrater-reliability will be determined for IB and MB bias scores.

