#### Sample size

As research on cognitive biases in adolescents with AN is very scarce we had to rely on results in adult AN samples for our sample size calculation [via G*Power; 63]. The aim of the present study is to investigate whether adolescents with AN show attention, interpretation, and memory biases. With regard to attention biases for ED-related information (i.e., body-related stimuli), a meta-analysis [15] reported a medium-sized effect (Glass' *g* = 0.5) for the group difference between patients with AN and HCs. Regarding attention biases for non-ED-related information, studies reported small [*d* ≤ 0.3; 26–28, 31, 32] to large [*d* ≥ 1.1; 23, 24] effects. With respect to interpretation biases, large effects (*d* ≥ 1.5) were reported for ED-specific [12, 18] as well as non-ED-specific biases [29]. A large effect was also reported for ED-specific memory biases [*d* = 0.8; 21]. In order to detect medium to large (*η*_*p*_^2^ = 0.08)^3^ main effects of the factor Group with an α of 0.05 and a power of 0.80 in a multi-factorial analysis of variance (ANOVA) with three groups, a sample size of *N* = 87 subjects is required. Furthermore, we want to examine to what extent these cognitive biases are specific for ED-related information and expect specificity of biases to translate as Group × Content interactions in the multi-factorial ANOVAs. None of the previous studies reported an effect size for such an interaction. If a small to medium-sized effect is assumed (*η*_*p*_^2^ = 0.03), a sample size of *N* = 81 subjects is necessary to detect the interaction. Since effects might be smaller in adolescent patients and experience shows that some subjects will have to be excluded from the analysis due to insufficient data quality in the experimental paradigms that we apply (see below for criteria), we aim for a total sample size of at least 105 subjects, *n* = 35 per group to ensure sufficient power.

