#### Stimuli

Stimuli consist of 70 scrambled sentences: 28 EDR emotional sentences (e.g., “my fat bottom find attractive I”), 28 NED emotional sentences (e.g. “total I winner a loser am”), and 14 neutral sentences (e.g., “I exciting watching funny movies like”). All sentences contain six words and have two possible solutions. Emotional sentences include one positive target word (“attractive”, “winner”) which can be used to build a positive solution (“I find my bottom attractive”, “I am a total winner”) and one negative target word (“fat”, “loser”) which can be used to build a negative solution (”I find my bottom fat”, “I am a total loser”). The EDR emotional stimuli are based on the stimulus set developed by Brockmeyer et al. [12], which was adapted and extended. They consist of self-referent sentences related to the evaluation of one’s body and physical appearance. The NED emotional stimuli are based on the original stimulus set developed by Wenzlaff and Bates [51], which was translated into German [74], extended, and adapted. They consist of self-referent sentences involving self-evaluation that is not related to body, weight, or appearance. A similar stimulus set has already used in previous studies in youth [54, 55]. Neutral sentences are also self-referent but do not involve any positive or negative evaluation of oneself. As such, both solutions are emotionally neutral. The stimuli are constructed in such a way that they include no negations and the target words are emotional words corresponding in valence to the respective solution (i.e., positive words correspond to positive solutions and negative words correspond to negative solutions). Target words are matched for length and frequency in the German language across the stimulus set.^4^ In line with Everaert et al. [50], word position within each sentence is randomized with target words not allowed next to each other or in the first or last position and counterbalanced whether the positive or negative target word is presented first.

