**Fig. 1 Fig1:**
[figure not shown]
Example of a NED emotional SST trial and overview of the experimental procedure

Trials are randomly divided into seven blocks of ten, each containing four ED-related emotional trials, four non-ED-related emotional trials, and two neutral trials. Trials are presented in a random order within blocks and blocks are also presented in a random order. Before the first block, participants complete five neutral practice trials to familiarize themselves with the task. Similarly to earlier studies [e.g., 50, 52] a cognitive load procedure is included to prevent deliberate response strategies: Before each block, a 5-digit number is presented for 5000 ms which has to be memorized and recalled at the end of the block.

After the SST a filler task (an unrelated task consisting of watching pictures) lasting approximately 15 min is administered [e.g., 76]. Filler tasks serve to displace the content from the working memory so participants have to retrieve the content from episodic memory during a subsequent free recall [77]. Afterwards an incidental free recall test is administered. Participants are asked to recall as many of the sentences they had previously formed as possible and write them on a piece of paper. Up to ten minutes are allowed for this task but the participants are not informed about the time limit.

Attention biases are assessed via eye movement registration during the stimulus display parts of the trials while interpretation biases are derived from the behavioural results, i.e., the sentences the participants construct in the task. Memory biases are measured with the free recall test at the end of the experimental paradigm (see Fig. 1).

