### Analyses

#### Data processing and outcome variables

Participants’ responses (i.e., the sentences they built in the SST and the sentences they remembered in the free recall test) will be rated as correct or incorrect according to predefined criteria by two independent raters. Trials in which no grammatically correct sentence is built (time-out or incorrect sentence) will be excluded from the analyses. Participants with a correct sentence rate of three standard-deviations (*SD*) below the mean (in the SST) will be identified as outliers in terms of accuracy [e.g., 55] and excluded from all analyses.

For analysis of attention biases, we will additionally exclude trials with poor eye-tracking data quality [i.e., trials in which the total dwell time is less than 75% of the presentation time due to excessive blinks, missing data, or participants not looking at the screen; 79, 80]. Subsequently, participants with insufficient remaining trials [less than 75%; e.g., 80] and participants with systematic calibration errors (identified by visual inspection) will be excluded from the analysis of attention biases. Attention bias scores will be calculated by dividing the percentage of dwell time on negative target words (i.e., on the areas of interest around those words) by the sum of percentage of dwell times on negative and positive target words, so that a higher value indicates a more negative attention bias [similar to 50]. Separate scores for EDR and NED sentences will be calculated, resulting in an AB_EDR_ and an AB_NED_ score.

For analysis of the interpretation bias, the correctly unscrambled emotional sentences will be categorized as either positive or negative. Two interpretation bias scores will be calculated: IB_EDR_ reflects the proportion of negatively resolved sentences from the total number of correctly resolved EDR sentences while IB_NED_ reflects the proportion of negatively resolved sentences from the total number of correctly resolved NED sentences [50].

For analysis of memory biases, memory bias scores (MB_EDR_ and MB_NED_) will be calculated similarly: as the proportion of correctly remembered negative sentences from the total number of correctly remembered EDR or NED sentences [50], respectively.

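### One odd-even split decides whether a bias score is analysed and reported; averaging over many random splits would make that decision modestly more stable when reliability is near 0.7

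*Protocol article*

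**What the plan says.** The Reliability section fixes both the method and its consequence. The method is one split: "Split-half reliability of the bias scores will be assessed by correlating bias scores based on odd versus even trials". The consequence is a gate: "only bias scores with at least acceptable reliability (Spearman-Brown corrected reliability > 0.7) will be analyzed and reported". The section gives no averaging over splits and no interval for the coefficient.

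Six scores face the gate: attention, interpretation and memory, each for eating-disorder-related (EDR) and non-eating-disorder-related (NED) sentences. Under Stimuli there are "28 EDR emotional sentences" and the same number of NED sentences. Data processing and outcome variables removes some of these: "Trials in which no grammatically correct sentence is built (time-out or incorrect sentence) will be excluded from the analyses". Under Sample size, "we aim for a total sample size of at least 105 subjects".

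Analyses of hypotheses tests each level of processing with a repeated-measures ANOVA that has Content (EDR, NED) as the within-subject factor, so it needs both scores of that level.

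**The concern.** Twenty-eight trials can be halved in very many ways, and each gives a somewhat different coefficient from the same data. Odd versus even is one of them. As a descriptive statistic that would hardly matter. Here the number decides whether an outcome is analysed and published, so variation due only to the choice of halves can carry a score across 0.7 in either direction. If one content score of a level fails, the Group × Content interaction, which is where the hypotheses are expected to show, cannot be tested for that level.

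**Working it through.** **The plan's own figures.** The document states no figure for the stability of the reliability estimate. Its sample sizes do reproduce with three groups, two measurements and an assumed correlation of 0.5 between them: N = 87 gives power 0.804 for the Group effect, and N = 81 gives power 0.800 for the interaction. They enter here only as background to the number of participants.

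**Inputs from the document.** 105 participants, 28 trials per content type, one split, cut-off 0.7.

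**Assumptions.** Parallel trials; true full-length reliability R varied from 0.60 to 0.80; no lost trials in the base case.

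**Formulas.**
- Corrected coefficient: 2r/(1 + r), where r is the correlation between halves. The cut-off of 0.7 corresponds to r = 0.7/(2 − 0.7) = 0.54.
- Single-trial intraclass correlation used to generate data: R/(k − (k − 1)R). For k = 28 and R = 0.70 this is 0.70/(28 − 18.9) = 0.077.

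**Simulation.** In each simulated study, one random split is compared with the mean over many other splits of the same data, both judged against 0.7. A wrong decision means passing when R is below 0.7 or failing when R is above it. Rows 0.66, 0.69, 0.70, 0.71 and 0.73 use 3,000 studies each; rows 0.75 and 0.80 use 600.

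| R | opposite sides of 0.7 | SD, one split | SD, average | wrong, one split | wrong, average |
|---|---|---|---|---|---|
| 0.66 | 19% | 0.070 | 0.051 | 28% | 19% |
| 0.69 | 24% | 0.065 | 0.047 | 44% | 41% |
| 0.70 | 25% | 0.062 | 0.046 | – | – |
| 0.71 | 24% | 0.059 | 0.043 | 41% | 40% |
| 0.73 | 21% | 0.055 | 0.041 | 30% | 24% |
| 0.75 | 14% | 0.051 | 0.037 | 18% | 11% |
| 0.80 | 2% | 0.040 | 0.031 | 2% | 1% |

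A separate simulation of wrong decisions gave 27% against 16% at 0.66, 44% against 41% at 0.69, 37% against 34% at 0.72 and 17% against 10% at 0.75. The differences are 11, 3, 3 and 7 percentage points. Immediately beside the cut-off the gain is close to nil, as the 0.71 row shows.

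**Where the variance comes from.** At R = 0.70 the split contributes 0.062² − 0.046² = 0.0017, an SD of about 0.042. This agrees with the SD of 0.041 seen across splits of the same data. It is 0.0017/0.0038, or about 45% of the total variance. The rest is sampling error between participants, which no choice of split removes.

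**Sensitivity at R = 0.70.** Disagreement is 22-25% with binary outcomes (mean negative proportion 0.3), 23-25% with 87 participants and 24-25% with 8 scored sentences. With 15% of trials lost it is 20-21%, the loss having lowered the average coefficient to about 0.66. Splits drawn per participant and one fixed split for everyone gave similar results (25% and 20% in the 600-study runs).

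**Memory.** The memory score rests on recalled sentences, and the document gives no recall count. If a girl recalls m sentences per content on average and the two halves are Poisson with mean m/2, the chance that at least one half is empty is 1 − (1 − e^(−m/2))². For assumed m = 3, 5 and 7 this is 40%, 16% and 6%.

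**The case against.** The odd-even rule is pre-specified, conventional and cited to earlier studies, so it leaves little room to pick a favourable split. That stands: the issue is instability, not selection after seeing the data.

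The disagreement rate compares one noisy estimate with another. A reader might infer that about a quarter of studies reach a wrong decision because of the split. The table does not support that. Close to 0.7 both methods are often wrong, mainly because 105 girls cannot place a reliability precisely against a point cut-off.

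The effect is also confined to a narrow band, and nothing in the document places a score there. The Background calls the task's split-half reliability acceptable to excellent, particularly for interpretation bias. For attention and memory it gives no figure, so their exposure is unknown.

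Two stronger readings should be set aside. First, because "Trials are presented in a random order within blocks and blocks are also presented in a random order", one might infer that an odd-even split mixes EDR and NED sentences unevenly. But the bias scores are defined separately by content, and the natural reading is odd versus even within each content type. Second, one might infer that a memory half will often be empty. That depends entirely on recall counts the document does not give, and random splits would produce empty halves too.

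**Conclusion.** The concern holds in a limited form. For a true reliability of about 0.66 to 0.73, one split and the average split disagree about the gate in roughly 18-25% of simulated studies. Averaging reduces the SD of the estimate at 0.70 from about 0.06 to about 0.045. The practical benefit is about 3 to 11 percentage points fewer wrong decisions at the four levels from 0.66 to 0.75 examined in the separate simulation, nearly none right beside 0.7, and little at 0.80 or above. These figures assume parallel trials and the stated 105 participants and 28 trials. A cut-off applied to a point estimate stays uncertain even after the change. It is a cheap gain in precision that the sponsor could adopt; leaving the rule as it is would not invalidate the study.

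**What to change.** Before the outcome data are examined, replace the odd-even split with the mean Spearman-Brown coefficient over many random splits (for example 5,000), drawn within each content type. Report it with a 95% interval and use the mean for the 0.7 rule. For memory, also report how many girls can be scored in both halves, since random splitting does not prevent empty ones.

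The cost is a documented amendment, because data collection is already under way according to Study status, and a short script, possibly outside SPSS. No additional data are needed.

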#### Analyses of hypotheses

Statistical analysis of the data will be performed using IBM SPSS Statistics. Group differences in demographic and clinical characteristics (age, IQ, body-mass-index as well as ED, depression, and anxiety symptoms) and other questionnaire scores (self-esteem, body dissatisfaction, and social appearance anxiety) will be examined using univariate ANOVAs with the between-subjects factor Group (3: AN, CC, HC) and follow-up *t*-tests. The hypotheses will be addressed with separate analyses for attention, interpretation, and memory biases. Repeated-measures ANOVAs on bias scores will be performed with within-subject factor Content (2: EDR, NED) and between-subjects factor Group (3: AN, CC, HC). Significant main effects and interactions will be followed up by post-hoc ANOVAs and *t*-tests. We expect our hypotheses (hypothesis 1 regarding ED-related biases: AN > CC = HC; hypothesis 2 regarding non-ED-related biases: CC ≥ AN > HC) to translate as Group × Content interactions in the ANOVAs and corresponding results in the post-hoc tests. Associations between bias scores and psychopathology (questionnaire measures) will be assessed via Pearson’s correlations. For all analyses, the significance level will be set to *p* = 0.05 (two-tailed) and adjusted according to the Bonferroni–Holm procedure [85] when multiple post-hoc comparisons are performed. Effect sizes will be reported for all significant effects: *η*_*p*_^2^ and *η*_*G*_^2^ for ANOVA effects and Cohen’s *d*_*s*_ for between-group *t*-tests, as suggested by Lakens [86]. In addition to testing our hypotheses, we will explore to what extent cognitive biases are related to participants’ psychopathology by calculating correlations between bias scores and ED, depression, and anxiety symptoms as well self-esteem, body dissatisfaction, and social appearance anxiety.

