An additional limitation of the previous literature is that most studies on cognitive biases in AN have been performed in adult populations. Regarding interpretation and memory biases, no studies to date have compared adolescents with AN to healthy adolescents.^1^ However, the transfer of results on cognitive biases obtained in studies on adults to adolescents is problematic as major cognitive and affective development is ongoing during adolescence [35–37]. Therefore, dysfunctional cognitions might either play a smaller role in adolescent than adult AN as cognitive patterns might not have evolved into stable, trait-like “cognitive styles” yet [as suggested for depression, e.g., 38]. Alternatively, young people might be particularly susceptible to negative cues in ambiguous emotional information due to brain maturation and hormonal changes associated with an enhanced emotional sensitivity [see e.g., 39], resulting in more pronounced cognitive biases. Considering also that the incidence of AN is highest during adolescence [e.g., 3], it is particularly relevant to investigate which dysfunctional cognitions are already present at this relatively early stage of the disorder. Cognitive biases are not only suggested to be involved in the development and maintenance of AN [e.g., 8, 9], but can also be experimentally manipulated in adults [e.g., 40–43] as well as adolescents [e.g., 34] with AN or other EDs. Therefore, knowledge about cognitive biases in adolescents with AN may help to develop interventions that step in early in the course of the illness, change underlying cognitive vulnerabilities before the illness takes a chronic course, and optimize existing therapies. Therefore, the aim of the present study is to systematically investigate whether adolescents with AN show cognitive biases in attention, interpretation, and memory and to examine to what extent these biases are specific for ED-related information and to what extent they are general negative biases (content-specificity).

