#### Recruitment

Participants in the AN and CC groups are recruited through the Department of Child and Adolescent Psychiatry, Psychosomatics and Psychotherapy of the LMU University Hospital Munich. Potentially eligible in- and outpatients and their parents/legal custodians are approached by a member of the study team and provided a comprehensive explanation of the study procedures. Participants in the HC group are recruited via previous studies in which they had participated as healthy controls. Families receive a letter with information about the study and an invitation to participate. Participants receive a reimbursement of €30 as shopping vouchers (e.g., for Amazon).

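### Age is compared between the non-randomised groups without consequence and left out of the bias models, so an age difference would bias the between-group contrasts behind hypotheses 1a to 2c

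*Protocol article*

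**What the plan says.** - **Design and groups** (Methods; Participants). The study is a cross-sectional comparison of 35 girls with AN, 35 clinical controls and 35 healthy controls, all aged 12 to 18. Group membership follows from diagnosis. The common limits are female sex, the age range and an IQ of at least 85.
- **Sources** (Recruitment). AN and clinical-control participants are in- and outpatients of one hospital department. For the third group: "Participants in the HC group are recruited via previous studies in which they had participated as healthy controls". No matching of participants on age or IQ is described; the only matching mentioned concerns the target words (Stimuli).
- **Handling of age** (Analyses of hypotheses). The article will examine "Group differences in demographic and clinical characteristics (age, IQ, body-mass-index as well as ED, depression, and anxiety symptoms", and the other questionnaire scores, with univariate ANOVAs and follow-up t-tests. It does not say what follows from a difference.
- **Hypothesis models** (same section). Each of attention, interpretation and memory gets a repeated-measures ANOVA with Content (2 levels) and Group (3 levels), followed by post-hoc ANOVAs and t-tests. No covariate is named.
- **Relevance of age** (Background). Adult findings are said not to transfer readily because "major cognitive and affective development is ongoing during adolescence"; biases could turn out weaker or stronger for that reason.
- **Status of the plan** (Discussion). Having settled data processing and analysis in advance is listed as a strength.

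**The concern.** Without randomisation, nothing in the design makes the three groups alike in age. Clinic patients and volunteers from earlier studies reach the study by different routes, so their age distributions within 12 to 18 may well differ. If a bias score also varies with age, part of the age difference appears as a group difference.

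Two features of the plan leave this open. The model for the hypotheses is written out and contains no age term, so this is more than a detail left to a fuller document. The one step that looks at age is a significance test, which is a weak detector of a moderate imbalance at 35 per group and leads to no action.

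At stake are the contrasts that decide hypotheses 1a to 2c: AN, clinical controls and healthy controls compared within each content. Predictions of no difference (1c) or of a similar or smaller bias in AN than in clinical controls (2b) are sensitive too, since a modest shift can create or hide the predicted pattern.

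**Working it through.** **1. The plan's own sample sizes.** The inputs in Sample size are partial eta squared 0.08 for Group and 0.03 for Group × Content, "with an α of 0.05 and a power of 0.80 in a multi-factorial analysis of variance (ANOVA) with three groups". The article gives no correlation between the two content scores; ρ = 0.5 is assumed here. With f² = η²/(1 − η²), three groups and two measures:

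- Group: f² = 0.08/0.92 = 0.0870; λ = N·f²·2/(1 + ρ) = 87 × 0.0870 × 2/1.5 = 10.1; df 2 and 84; power 0.804. This matches "a sample size of *N* = 87 subjects is required".
- Group × Content: f² = 0.03/0.97 = 0.0309; λ = N·f²·2/(1 − ρ) = 81 × 0.0309 × 2/0.5 = 10.0; df 2 and 78; power 0.800. This matches the stated 81.

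Both figures reproduce. At N = 105 the powers are 0.88 and 0.90. The sample size is not in dispute.

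**2. What an age gap does to an unadjusted group contrast.** Let D be the age gap between two groups in within-group SDs and r the within-group correlation of age with the bias score. With no true difference, the expected standardised difference is d = r × D. The article gives neither D nor r; both are assumptions. If ages were spread evenly over the range, the SD would be 1.7 years (12 to 18) to 2.0 years (12 to 19, counting all 18-year-olds), so D = 0.5 is about 0.9 to 1.0 year.

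For a two-sided t-test at 0.05 with 35 per group (df 68, noncentrality d × √(35/2) = 4.18d), before any Holm adjustment:

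| r | D | spurious d | false-positive rate |
|---|---|---|---|
| 0.1 | 0.25 | 0.025 | 5.1% |
| 0.1 | 0.5 | 0.05 | 5.5% |
| 0.2 | 0.5 | 0.10 | 7.0% |
| 0.3 | 0.5 | 0.15 | 9.5% |
| 0.4 | 0.5 | 0.20 | 13.1% |
| 0.3 | 1.0 | 0.30 | 23.6% |
| 0.4 | 1.0 | 0.40 | 37.8% |

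Against the effects cited in Sample size, 0.05 to 0.20 is 10 to 40% of the 0.5 for ED-related attention, 6 to 25% of the 0.8 for memory, and 3 to 13% of the 1.5 for interpretation.

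**3. What it does to the interaction.** With both scores scaled to unit SD, the spurious interaction contrast between two groups is (r_EDR − r_NED) × D. If r_EDR = r_NED, it is zero whatever the age gap. If, say, r_EDR = 0.3 and r_NED = 0.1 with D = 0.5, it is 0.2 × 0.5 = 0.10.

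**4. Whether the planned age comparison would notice.** For D = 0.5 between two groups of 35, the t-test has noncentrality 0.5 × 4.18 = 2.09 and power 0.54. If one of the three groups is shifted by D, f² = 2D²/9 = 0.0556, λ = 105 × 0.0556 = 5.83, df 2 and 102, and the power is 0.56. For D = 0.25, 0.75 and 1.0 the F-test has power 0.17, 0.90 and 0.99.

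**5. What adjustment costs.** With age balanced across groups, f² becomes f²/(1 − r²), with r now the correlation of age with the between-subject score, and the error df become N − 4. At N = 105, power for Group is 0.88, 0.89, 0.91 and 0.93 for r = 0, 0.2, 0.3 and 0.4.

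**The case against.** The best counter-argument is that the article expects its hypotheses to show up as Group × Content interactions. Content varies within subjects, so an age effect common to both contents cancels there. That stands. It does not protect the hypotheses themselves, which are between-group statements within each content and are settled by the post-hoc tests.

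A reader might infer more than the document supports:

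- **That the groups are unmatched.** The article only describes no matching. How controls were picked from earlier studies may be recorded in a fuller protocol.
- **That the plan itself asserts an age gradient.** The Background argues that adult results may not carry over and offers two opposite possibilities. It claims no trend within 12 to 18, so the direction of any bias is unknown.
- **That reading or reasoning ability distorts a timed task.** All three scores are relative measures of negative against positive material, and time-outs and incorrect sentences are excluded. General slowness does not by itself shift such a ratio. The case for IQ is weaker than for age.
- **That adjustment sharpens every test.** The interaction's error shrinks only through an age effect that differs by content.

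The size is also hypothetical. Strong inflation (24 to 38%) needs a gap of 1 SD with r of 0.3 to 0.4, and the age ANOVA would flag such a gap 99% of the time. But a flagged gap has no stated consequence, and a gap of 0.5 SD would go unflagged in more than four of ten studies.

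**Conclusion.** The point holds for age, and for the Group main effect and the post-hoc between-group contrasts within each content. The interaction is at risk only through a content-specific age effect. Under the assumed gap of 0.5 SD and correlations of 0.1 to 0.4, the spurious difference is 0.05 to 0.20 SD and the unadjusted false-positive rate 5.5 to 13.1%. This matters most for attention, where the cited ED-related effect is 0.5, and least for interpretation. If the groups turn out alike in age, or the scores do not vary with age, there is no bias. The figures are illustrations, not estimates of what this study will show. The flaw does not invalidate the design, but it leaves open a foreseeable rival explanation that the analysis can address with data already collected.

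**What to change.** State in the analysis plan, before the bias data are analysed, that:

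- each of the three repeated-measures models includes age, centred at the grand mean, and the age × Content interaction;
- post-hoc group comparisons within each content are age-adjusted contrasts from these models, with the Bonferroni–Holm adjustment as planned;
- this applies whether or not the age comparison is significant;
- unadjusted results are reported alongside.

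IQ may be added as an optional sensitivity analysis. BMI and symptom scores should not be adjusted for, because they are part of the diagnosis or follow from it. Age matching would serve the same purpose, but recruitment was already under way when the article was written, so it could at best be applied to later participants.

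The cost is wording and one or two error degrees of freedom. No larger sample is needed if the groups are reasonably balanced on age; power is lost if they differ strongly. The adjustment also assumes a common linear age slope across groups, which should be stated as a limitation.

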
In line with findings in adult AN patients it is hypothesized that adolescents with AN will show more pronounced negative cognitive biases compared to healthy adolescents (HC group) for both ED-related information (hypothesis 1a) [e.g., 11, 12, 20] and non-ED-related information (hypothesis 2a) [e.g., 22, 29]. Furthermore, it is expected that adolescents with AN will show stronger biases for ED-related information than adolescents with depression or anxiety disorders (hypothesis 1b), whereas biases for non-ED-related stimuli will be similar or less pronounced in adolescents with AN compared to adolescents with depression or anxiety disorders (hypothesis 2b). Adolescents with depression or anxiety disorders (CC group) are not expected to differ from the HC group regarding ED-related biases (hypothesis 1c) but to show more pronounced negative biases for non-ED-related information than the HC group as well (hypothesis 2c) [in line with e.g., 47, 48]. In summary, for ED-related biases we expect the following pattern: AN > CC = HC (hypothesis 1) and for non-ED-related biases we expect: CC ≥ AN > HC (hypothesis 2). Thus, we expect specificity of biases to translate into differential results for the two types of content (i.e., Group × Content interactions in the analyses). In addition, we will explore to what extent cognitive biases are associated with participants’ psychopathology.

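### The predicted equalities (CC = HC, AN similar to CC) have no test that could support them, and no effect size is promised when those comparisons are non-significant

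*Protocol article*

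**What the plan says.** The last paragraph of the Background makes absence of a difference a numbered hypothesis: "Adolescents with depression or anxiety disorders (CC group) are not expected to differ from the HC group regarding ED-related biases (hypothesis 1c"). For the other content type, it predicts that "biases for non-ED-related stimuli will be similar or less pronounced in adolescents with AN compared to adolescents with depression or anxiety disorders (hypothesis 2b").

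Analyses of hypotheses restates both as orderings, "hypothesis 1 regarding ED-related biases: AN > CC = HC; hypothesis 2 regarding non-ED-related biases: CC ≥ AN > HC", and expects them "to translate as Group × Content interactions in the ANOVAs and corresponding results in the post-hoc tests". The follow-up tools are named: "Significant main effects and interactions will be followed up by post-hoc ANOVAs and *t*-tests". The significance level is "0.05 (two-tailed) and adjusted according to the Bonferroni–Holm procedure" for multiple post-hoc comparisons. On reporting, the section says "Effect sizes will be reported for all significant effects".

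The article names no equivalence margin, confidence-interval rule or Bayesian test. Sample size bases its calculation on the Group main effect and the Group × Content interaction, not on any pairwise or equality statement.

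**The concern.** A two-tailed t-test can support AN > HC by rejecting the null hypothesis. It cannot support CC = HC, because a non-significant result arises both when the groups are alike and when the data are too imprecise to tell. Since no other tool is named, non-significance is the only post-hoc result that could correspond to 1c or to the similar part of 2b. The estimate and interval that would separate the two explanations are not promised for such results.

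The article itself gives a reason to doubt 1c. The Background says that negative body-related bias may reflect poor self-esteem, which occurs across disorders. A moderate CC–HC difference on eating-disorder-related bias is therefore the rival explanation. At stake is whether the study can say that clinical controls lack this bias, or only that it did not detect it.

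**Working it through.** **Inputs from the article.** 35 per group (Participants; Sample size); two-tailed 0.05 with Bonferroni–Holm (Analyses of hypotheses); α 0.05, power 0.80, η_p² = 0.08 for Group and 0.03 for the interaction, N = 87 and 81 (Sample size).

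**Assumptions.** Equal-variance two-sample t-tests; a Holm family of three pairwise comparisons per content type (the article does not define the family); differences in SD units; margins as shown, since the article gives none.

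**1. The plan's own figures.** Repeated-measures ANOVA, three groups, two measurements, within-subject correlation ρ = 0.5 (not stated; the value that reproduces both figures).
- Group: f² = 0.08/0.92 = 0.087; λ = f²·N·2/(1+ρ) = 0.087 × 87 × 1.333 ≈ 10.1; power 0.804. N = 87 is reproduced.
- Interaction: f² = 0.03/0.97 = 0.0309; λ = f²·N·2/(1−ρ) = 0.0309 × 81 × 4 ≈ 10.0; power 0.800. N = 81 is reproduced.

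The sample size is sound for what it was built to detect. It says nothing about precision for CC minus HC.

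**2. Precision of one pairwise contrast.** Half-width of the 95% CI = t(0.975; 68) × √(2/35) = 1.995 × 0.239 = 0.477 SD. With 29 per group (87/3), it is 2.003 × 0.263 = 0.526 SD.

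**3. Which Holm level applies.** Holm tests the smallest p-value at 0.05/3, the next at 0.05/2 and the largest at 0.05. If AN > CC and AN > HC are significant and CC–HC is not, CC–HC has the largest p-value and is judged at the full 0.05.

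**4. Chance that a real CC–HC difference is non-significant at 0.05.** Noncentral t, 68 degrees of freedom, noncentrality d·√(35/2).
- d = 0.4: noncentrality 1.67; non-significant 62% of the time.
- d = 0.5: noncentrality 2.09; non-significant 46% of the time.
- With 29 per group, d = 0.5: non-significant 54% of the time (1 − 0.465).

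**5. What a proper equality test could deliver at n = 35.** True difference 0, one-sided 0.05.
- Two one-sided tests (TOST) for 1c, by simulation: power 33% at ±0.5 SD, 60% at ±0.6, 79% at ±0.7.
- One-sided test that AN minus CC lies below 0.5 SD for 2b: noncentrality 0.5 × √(35/2) = 2.09; power 66%.

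**The case against.** Several stronger readings are tempting, and the article does not support them.

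- *Low power confirms the whole predicted pattern.* It does not. The pattern also needs significant AN > CC and AN > HC results and a Group × Content interaction, and low power works against all three. Simulated Holm-adjusted pairwise tests, ignoring the interaction, show this. With true means AN 1.0, CC 0.4 and HC 0 SD, the false pattern AN > CC = HC appears 20% of the time at 15 per group, 43% at 35 and 34% at 70. The relation is not monotone; only the isolated equality element gets easier with less data.
- *The Holm adjustment makes equality easier still.* Within the predicted pattern it does not, because CC–HC is then the last step, at the full 0.05. Miss rates computed at 0.05/3 do not apply there.
- *Disorder-specificity rests on CC = HC.* It rests mainly on 1b (AN > CC) and the interaction, which are ordinary superiority tests. 1c plays a supporting part.
- *All of 2b depends on non-significance.* A significant CC > AN would also support it. Only the similar part is exposed.

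It can also be said that the article never states that a non-significant result will be read as equality, that its reporting sentence sets a minimum rather than a prohibition, and that the data will be made public. All true. But the article makes equality a hypothesis, expects matching post-hoc results and offers nothing else that could match. Public data let others compute the contrasts; they do not fix in advance how the authors will conclude.

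Finally, a margin of 0.5 SD is open to dispute. In Sample size that value is the AN–HC effect for attention bias, so using it for CC–HC could call groups equal when they differ by nearly that amount. This objection stands, and the point does not depend on any particular margin.

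**Conclusion.** The point holds for the equality parts alone: 1c and the similar part of 2b. As written, neither can be supported by the named tests, and the figures needed to judge them are not promised. At 35 per group, the interval is about ±0.48 SD, and a true CC–HC difference of 0.4 or 0.5 SD would go undetected 62% or 46% of the time. Exclusions for data quality, which the article expects without giving a rate, would raise these figures.

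The numbers assume t-tests with equal variances and CC–HC as the last of three Holm steps. Hypotheses 1a, 1b, 2a and 2c and the interaction test are unaffected.

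**What to change.** 1. Replace the reporting sentence with one promising effect sizes and 95% confidence intervals for every prespecified group contrast, significant or not.
2. State that a non-significant CC–HC contrast (1c) or AN–CC contrast (2b) will be reported as no difference shown, not as support for equality or similarity.
3. Only if the authors want to claim equality: prespecify an equivalence test for 1c and a one-sided margin test for 2b, justify the margin, and state the power at the planned sample size.

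Items 1 and 2 change wording only, need no new data, and can be made while data collection is ongoing. The price is that the equality claims become harder to make. Item 3 is a trade-off: among the equivalence margins shown, only ±0.7 SD comes close to 80% power (79%) with 35 per group, and a margin that wide may be hard to defend.
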